### 3.2 Participants and recruitment

The focus of this study is on the residents of a specific commune within the Colonche Parish, located in the Santa Elena province of Ecuador. The participant pool consists of families with an average monthly income of $463.93, a figure significantly lower than the cost of the Ecuadorian basic necessities basket, estimated at $789.57 (36, 37). The predominant educational attainment among community members is up to the primary level, facilitated by the region's publicly funded educational system. Each commune is home to ~3,875 individuals, distributed across 968 households. In addressing the needs of this community, the study aims to provide direct access to food for all participating families, leveraging the coastal commune's resources to enhance their food security and nutritional wellbeing.

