### 3.4 Sample size

A total of 968 families were considered as the research units in this study. Therefore, considering a margin of error of 5% and a confidence level of 95%, the estimated sample size before considering the finite population correction was approximately 384, according to Equation 1 where n is the sample size, Z is the Z-score associated (1.96) with the desired confidence level (95%), p is the estimated proportion of the attribute present in the population (0.5), and E is the margin of error (5%). After applying finite population correction, the estimated sample size was reduced to 276. This adjustment is made because the population is relatively small, and the correction helps avoid overestimating the required sample size. The sample of families in each commune is 300 because attrition is expected. The heads of the household will be surveyed regarding the nutritional, socioeconomic, and health situation of the family. The primary sampling unit for this study is the household (family unit), with a total sample size of 300 families. Within each family, specific questionnaires will be administered based on the nature of the assessment. The *Household Food Insecurity Access Scale (HFIAS)* will be completed by the head of the household to capture food security at the family level. For health and quality of life assessments, individual adult members will complete the *Short Form-36 Health Survey (SF-36)* and the *World Health Organization Quality of Life (WHOQOL-100)* questionnaire to evaluate personal health and quality of life outcomes. Additionally, the *Pediatric Quality of Life Inventory (PedsQL)* will be administered to caregivers of children to assess child health-related quality of life. This approach ensures comprehensive measurement across family and individual levels, providing both household-level insights and individual health metrics.

Formula for sample size estimation.

(1)
$$\begin{array}{l} n=\frac{Z^{2}\times p\times \left(1-p\right)}{E^{2}} \end{array}$$

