### 3.10 Statistical analysis

All statistical analyses will be performed using Stata 18.0 (44). Descriptive statistics will be calculated for both qualitative (e.g., categorical) and quantitative (e.g., continuous) data. Categorical variables, such as employment status or food security, will be summarized using frequencies and percentages, while continuous variables, such as household income or nutritional status (e.g., BMI), will be described using means and standard deviations for normally distributed data, or medians and interquartile ranges for non-normally distributed data.

For hypothesis testing, categorical variables like food security (measured as secure/insecure) and employment status (e.g., employed/unemployed) will be compared between the intervention and control groups using Chi-square tests or Fisher's exact tests, depending on sample sizes. For continuous variables, such as changes in household income or nutritional status (e.g., BMI, dietary diversity scores), Student's *t*-tests will be used if the data are normally distributed. If normality assumptions are violated, Mann-Whitney U tests will be applied instead.

To evaluate changes over time within the same group (e.g., baseline to 6 months), paired *t*-tests will be used for normally distributed continuous variables, such as income or BMI, while Wilcoxon signed-rank tests will be used for non-normally distributed variables. For categorical variables like food security status over time, McNemar's test will be applied.

Regarding regression models, linear regression will be used to assess continuous outcomes such as household income levels, nutritional status (BMI), or dietary diversity scores. Logistic regression will be applied to binary outcomes, such as food security (secure/insecure) or whether participants report improved health (yes/no). For outcomes with multiple categories, such as levels of health perception (good, fair, poor) or employment status (employed, unemployed, seeking work), multinomial logistic regression will be used.

To account for repeated measures over time (e.g., baseline, 6 months, and 12 months post-intervention), mixed-effects models (both linear and logistic) will be employed. These models will allow us to assess the effect of the intervention across different time points while controlling for intra-individual correlations. All hypothesis tests will be two-tailed, and a *p* < 0.05 will be considered statistically significant.

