To align with the nature of the data, nutritional and health status variables will be analyzed at the individual level, allowing us to capture specific health outcomes for each family member. Socioeconomic variables, including food security (measured by the Household Food Insecurity Access Scale [HFIAS]) and dietary diversity, will be evaluated at the family level. This approach enables a comprehensive analysis by distinguishing between individual health measures and collective socioeconomic conditions.

For older adult participants, the *Mini Nutritional Assessment (MNA)* will be used to assess undernutrition risk. For all other participants, individual nutritional status will be determined through anthropometric measurements (weight, height, and age). Household-level dietary diversity will be measured with a dietary diversity questionnaire, enabling us to capture a broader picture of household nutritional intake.

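### Section 3.10 ignores correlation between members of the same household, so standard errors are too small for any outcome with more than one respondent per household

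*Protocol article*

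**What the plan says.** Section 3.4 defines the sampling unit: "The primary sampling unit for this study is the household (family unit), with a total sample size of 300 families". It also states: "The sample of families in each commune is 300 because attrition is expected". Whichever count is meant, families are sampled and people are reached through them.

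Measurement then moves to the person. Section 3.4 says: "For health and quality of life assessments, individual adult members will complete the" SF-36 and WHOQOL-100. PedsQL "will be administered to caregivers of children to assess child health-related quality of life". Sections 3.5.1 and 3.10 reserve the MNA for older adults and give everyone else individual anthropometry. Section 3.10 fixes the unit of analysis: "nutritional and health status variables will be analyzed at the individual level, allowing us to capture specific health outcomes for each family member". Food security and dietary diversity stay at family level.

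For between-group comparisons, section 3.10 names Chi-square or Fisher tests, t-tests or Mann-Whitney tests, and linear, logistic and multinomial regression. For change within a group it names paired t, Wilcoxon signed-rank and McNemar tests. Mixed-effects models are introduced for repeated measures and described as working "while controlling for intra-individual correlations". The article mentions no household random effect, household-clustered variance or design effect.

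**The concern.** People in one household eat from the same supply, live on the same income and share an environment. The protocol itself treats food security and dietary diversity as properties of the family. Body mass, general health and quality of life are therefore likely to be positively correlated among relatives.

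Whole communes are assigned, so all members of a household fall in the same arm. Correlation among relatives then adds to the variance of the arm comparison, and a test that counts each person as a separate observation understates that variance. Confidence intervals are too narrow and the 5% error rate is exceeded. This reaches the anthropometric part of the primary outcome (nutritional status) and the individually measured part of the health-status secondary outcome. A mixed model with a person-level effect alone does not repair it, because it links the visits of one person and leaves siblings or spouses independent.

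**Working it through.** **The plan's own figure.** Section 3.4 uses Z = 1.96, p = 0.5, E = 0.05 and N = 968 households.

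- n0 = 1.96² × 0.5 × 0.5 / 0.05² = 384.16 (stated: about 384).
- Finite population correction: 384.16 / (1 + 383.16/968) = 275.2, which rounds up to 276 (stated: 276).

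The figures reproduce. They count households and contain no allowance for several people per household.

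**Inputs for the check.**

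- Household size, section 3.2: "Each commune is home to ~3,875 individuals, distributed across 968 households", so 3,875 / 968 = 4.0 people of all ages.
- Respondents per household for one outcome, m: not given. I use 2, and 4 as the upper bound.
- Within-household ICC: not given. I assume 0.1, 0.2 and 0.4.
- Two-sided 5% tests, section 3.10.

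**Formulas.** Design effect DE = 1 + (m − 1) × ICC. The correct standard error is √DE times the naive one. Actual type I error = 2 × (1 − Φ(1.96/√DE)).

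| m | ICC (assumed) | DE | Correct SE / naive SE | Actual type I error |
|---|---|---|---|---|
| 1 | any | 1.0 | 1.00 | 5% |
| 2 | 0.1 | 1.1 | 1.05 | 6.2% |
| 2 | 0.2 | 1.2 | 1.10 | 7.4% |
| 2 | 0.4 | 1.4 | 1.18 | 9.8% |
| 4 | 0.1 | 1.3 | 1.14 | 8.6% |
| 4 | 0.2 | 1.6 | 1.26 | 12.1% |
| 4 | 0.4 | 2.2 | 1.48 | 18.6% |

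**Simulation.** Naive t-tests with 300 households per arm, no commune effect and 4,000 runs rejected in 7.3% (m = 2, ICC 0.2), 8.3% (m = 4, ICC 0.1) and 12.9% (m = 4, ICC 0.2) of runs. This agrees with the formula.

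**Effective sample size.** At ICC 0.2, two respondents in each of 300 families give 600 people with the information of 600/1.2 = 500. Four give 1,200 people with the information of 1,200/1.6 = 750.

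**Which m applies to which outcome.** SF-36 and WHOQOL-100 are for adults, PedsQL for children and the MNA for older adults, so none of them covers all four members of an average household. Only anthropometry could approach four, and only if children's and adults' measures are pooled in one analysis, which the article does not say. Outcomes analysed once per family have m = 1.

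**The case against.** **Respondents per family are not settled.** Section 3.4 also says that heads of household will be surveyed about the family's nutrition, socioeconomic position and health, which points to one respondent. With one respondent there is no inflation. This stands as a conflict within the document. The instrument-level text in 3.4 and 3.5, and the per-member analysis in 3.10, nevertheless plainly provide for several people per family.

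**Four per household is too many for most outcomes.** A reader might take mean household size as the cluster size for every instrument, and so infer that the 9% to 19% range applies throughout. The age limits on the instruments rule that out. For adult questionnaires the two-respondent rows are the more relevant ones.

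**Not every outcome is affected.** A reader might also extend the point to the whole primary outcome and all secondary outcomes. Dietary diversity, food security and socioeconomic level are analysed by family. MNA and PedsQL escape wherever a household has one older adult or one child.

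**The ICC is assumed.** This is correct. Section 3.10 also applies the t-test to changes, and the ICC of a change need not equal that of a level. The direction of the error is secure if the ICC is positive, but its size is not.

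**The article does not exclude a household term.** This is true, and a full random-effects structure is often left to the SAP. But the article goes beyond silence: it fixes the individual as the unit, names tests that need independent observations, and names one source of correlation to control. The defence does not reach the t, Mann-Whitney and Chi-square tests at all.

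**The remedy leaves the main design limit in place.** This stands in full. One commune is treated against one (section 3.1) or two (section 3.3), and no household term separates commune differences from the intervention effect.

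**Conclusion.** The point holds for outcomes with more than one respondent per household: anthropometry, SF-36, WHOQOL-100, and PedsQL in families with several children. Analysed as section 3.10 is written, their standard errors are too small. Over the assumed ICC range of 0.1 to 0.4, the nominal 5% test runs at about 6% to 10% with two respondents and at about 9% to 19% with four, the latter only for anthropometry pooled over all ages. These rates isolate the household effect and assume no variation between communes.

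A reader might infer that modelling the household makes the 5% level valid. The documents do not support that while a single commune is treated. This point is secondary to the commune problem, but it is a distinct error that would remain if more communes were added.

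**What to change.** In section 3.10, for individual-level outcomes with more than one respondent per household:

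- Use mixed models with person nested in household, or household-clustered standard errors, in place of the t-test, Mann-Whitney, Chi-square or Fisher tests and unclustered regressions, and in place of the paired tests for change within a group. Where the contrast is change over time, clustered standard errors or a household-by-visit term are safer, because a household intercept that is constant over time cancels from change scores.
- Reword the mixed-model sentence so that it names household correlation as well as intra-individual correlation.
- State how many members per household supply each instrument, and reconcile the section 3.4 sentence on heads of household with per-member measurement.
- State that household adjustment does not address the comparison of one treated commune with one or two control communes.

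The change needs a household identifier on each record and a small change to the planned Stata models. The cost is wider intervals: over ICC 0.1 to 0.4, about 5% to 18% wider with two respondents and 14% to 48% with four (√DE − 1 from the table).

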### 3.11 Ethics and dissemination

The Kennedy Clinic's Institutional Review Board (IRB) in Guayaquil has granted approval for this study, under the code HCK-CEISH-2022-006. At every phase of the research, informed consent will be rigorously obtained and mandated, adhering to the ethical standards for research involving human participants. To ethically support the control group during the study, we will provide alternative community support measures, such as nutritional education and health assessments, to ensure both communities receive beneficial resources. Additionally, we have planned a delayed food forest intervention for the control group as soon as funding allows, ensuring that both communities ultimately benefit from the initiative. This approach has been designed in collaboration with community leaders to align with ethical standards and community expectations.

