## Abstract

Malnutrition is an escalating concern in low-and-middle-income countries (LMICs), including Ecuador, particularly within rural settings. To address this issue, food forests emerge as a promising intervention. This research protocol outlines a controlled intervention in the province of Santa Elena, aiming to evaluate the efficacy of a food forest in enhancing nutritional outcomes, with potential implications for broader replication. The study will be conducted in the Colonche Parish of Santa Elena Canton, where one commune will be randomly selected to receive the food forest intervention. In contrast, another similarly characterized commune, also randomly selected through cluster-based sampling, will serve as a control group, receiving no intervention. This randomized, comparative approach will enable a more precise assessment of the food forest's impact. Data collection will occur at three intervals: baseline, 6 months, and 12 months post-intervention. Comprehensive questionnaires will be employed to measure the food forest's influence on the communities' nutritional, economic, and health metrics, distinguishing between the intervention and control communes to elucidate the intervention's specific effects.

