## 3 Methods

### 3.1 Study design

This study employs a randomized community trial design to assess the impact of a novel Food Forest reforestation technique that emphasizes the use of endemic and food-producing species. The goal is to enhance food sovereignty among coastal families in the Santa Elena Province, Ecuador. This initiative, a collaborative effort by Nedetel and CECAPROF Corporación Ecuatoriana De Capacitación (two companies that serve the area), aims to address the dual challenges of malnutrition and low average family incomes in the region (33). Participants for the study will be recruited from rural areas within the Colonche Parish of the Santa Elena Canton, a geographical area detailed in Figure 1 (34, 35). The study randomly allocated one commune to receive the Food Forest intervention, while a similarly characterized commune was randomly assigned as a control group, receiving no intervention. This randomization process ensures that the study meets the criteria of a randomized community trial. In consideration of ethical concerns, we have planned a delayed intervention for the control group. After the study period, the control commune will also receive the food forest intervention, contingent on securing additional funding. This phased approach allows for a scientifically rigorous assessment of the intervention's effects while ensuring that both communities ultimately benefit from the food forest initiative. The intervention strategy was developed based on insights from prior research, supplemented by consultations and interviews with experts in nutrition and reforestation, ensuring that the Food Forest initiative is ecologically viable and tailored to meet the nutritional and economic needs of the local communities involved.

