### 4.2 Content of intervention

The community's role in establishing and maintaining the food forest is structured through active participation in key phases of the project. Community members are involved from the onset in activities such as site preparation, planting, and periodic maintenance. Harvests are organized so that community members can collectively decide on usage, ensuring fair distribution and communal benefit. Regular meetings will also allow the community to provide input on project development, further strengthening local engagement and commitment to long-term maintenance.

The intervention comprises two key activities (plantations and reforestation workshops), conceived and implemented by Nedetel and CECAPROF, within the territories of the Colonche Parish communes. Designed to run concurrently, these activities span in total 5 years, allowing for a synchronized approach. This strategic implementation aims to address malnutrition and enhance the average family income in Santa Elena Province, contributing to overall community wellbeing.

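### The control is described as untreated but is promised nutritional education during the study; if only controls receive it, the trial does not estimate forest versus nothing

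*Protocol article*

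**What the plan says.** The Abstract says the comparison commune "will serve as a control group, receiving no intervention". Section 3.1 repeats this: "a similarly characterized commune was randomly assigned as a control group, receiving no intervention".

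Section 3.11 differs. It opens with the purpose and timing, "To ethically support the control group during the study", and continues "we will provide alternative community support measures, such as nutritional education and health assessments, to ensure both communities receive beneficial resources".

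On the other arm, section 4.2 states: "The intervention comprises two key activities (plantations and reforestation workshops". Section 4.1 adds training in agroecology. The workshop curriculum in section 4.2.2 covers seeds, nurseries, mapping, project planning and environmental education. None of these sections mentions nutritional education.

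On the controls' later access to a forest, section 3.1 says "After the study period, the control commune will also receive the food forest intervention, contingent on securing additional funding", while section 3.11 says "we have planned a delayed food forest intervention for the control group as soon as funding allows".

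**The concern.** The comparator fixes what the trial can conclude. A reader of the Abstract expects the effect of a food forest against no programme at all. Under section 3.11 the controls have a programme of their own, and its education component is aimed at the domain of the primary outcome: section 3.9.1 names dietary habits and quality of nutrition, and dietary diversity is in the first specific objective (section 2.2).

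If only controls receive the education, it is completely confounded with arm, and no analysis in section 3.10 can separate the two. A null result could then mean that the forest did nothing, or that forest and education did about equally well.

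The delayed forest is a second, smaller issue. If controls receive it before the last assessment used, the later visits no longer compare forest with no forest.

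**Working it through.** **1. Does the article give a figure from which the bias could be sized?** The only sample-size figure is in section 3.4, with inputs Z = 1.96, p = 0.5, E = 0.05 and N = 968 families.

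- Before correction: 1.96² × 0.5 × 0.5 / 0.05² = 384.16, against about 384 stated.
- Finite population correction: 384.16 / (1 + 383.16/968) = 275.2, rounded up to 276, as stated.

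Both figures reproduce. They give the precision of a single proportion and use no effect size, standard deviation, power or control condition, so they cannot size the bias.

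**2. What each arm receives, side by side.**

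| Component | Forest commune | Control |
|---|---|---|
| Plantations | yes (4.2, 4.2.1) | no |
| Agroecology training, reforestation workshops | yes (4.1, 4.2.2) | no |
| Nutritional education | not listed | none (Abstract, 3.1); yes, during the study (3.11) |
| Support health assessments | not listed | none (Abstract, 3.1); yes (3.11), content not given |

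The two entries for control in the last two rows cannot both stand. Control-only delivery of the education is an inference: the forest sections do not list it, and section 3.11 presents it as an alternative for controls.

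**3. What is estimated.** Let F be the effect of the forest package and E the effect of the education on a nutrition outcome, both against nothing, and assume that they add.

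- No education anywhere: F − 0 = F.
- Education in control only: F − E. As an estimate of F, its bias is −E.
- Education in all communes: (F + E) − E = F.

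The bias in the second case is zero only if E = 0. For a beneficial E smaller than F, the estimate moves towards no effect. Writing E = f × F, the remaining contrast is (1 − f) × F. With f assumed, since the article offers no value: f = 0.10 leaves 90%, f = 0.25 leaves 75% and f = 0.50 leaves 50%. This shows how the bias scales; it does not estimate it.

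**4. When the delayed forest matters.** The article has two follow-up schedules: 6 and 12 months (Abstract: "Data collection will occur at three intervals: baseline, 6 months, and 12 months post-intervention"; also section 3.10), and 1, 3 and 5 years (section 3.8). Section 4.3 calls the study period twelve months.

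- 6- and 12-month schedule, section 3.1 followed: the control forest comes after the last visit. No follow-up is affected.
- 1-, 3- and 5-year schedule, study period read as five years, section 3.1 followed: none is affected.
- 1-, 3- and 5-year schedule, study period read as twelve months: a control forest begun after month 12 satisfies both wordings, yet could precede the year 3 and year 5 visits.
- Section 3.11 taken alone: the start depends on funding only, and no visit is protected.

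**The case against.** The best defence is that the conflict is one of terms. Throughout the article the intervention is the forest, section 3.3 defines controls by their lack of access to it, and section 3.11 calls the education a support measure. On that reading an untreated control simply means one without a forest. This is fair as to wording, and section 3.3 indeed does not conflict with section 3.11. It does not remove the problem: a measure aimed at the primary outcome and apparently given to one arm is confounded with arm whatever it is called, and the Abstract still describes a different contrast.

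It can also be said that control-only delivery is nowhere stated. That stands, and is why the conclusion is conditional and the first request is for clarification. The reference in section 3.11 to both communities benefiting does not settle it, since it explains why controls are given something and does not say that the forest commune gets the education.

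Three stronger readings are tempting, and the article does not support them:

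- **That the health assessments also bias the comparison.** Their content is not given, and all participants have their health and nutrition assessed at every visit (section 3.8). No bias is shown.
- **That the delayed forest does bias the comparison.** Section 3.1 places it after the study period, and section 3.11 can be read consistently with that. The risk is conditional, as step 4 shows.
- **That the dilution can be expressed as a required increase in families.** No power is stated that could be preserved, and with one forest commune and one or two controls, more families would not remove the uncertainty between communes.

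Finally, a bias towards no effect would not by itself undermine a positive result. That is correct; the damage falls on a null or small result and on the size of the reported effect.

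**Conclusion.** The control condition is stated in two incompatible ways, and the article must settle which applies. If nutritional education reaches controls only and has any beneficial effect, the trial estimates forest versus nutritional education, and its estimate of forest versus nothing is biased towards no effect by the amount of the education's own effect. This rests on control-only delivery, inferred from what the forest sections leave out, and on the education having some effect. The bias cannot be quantified from the article. A reader might infer that the comparison could even favour control; that would need the education to outperform the forest, and no figure in the article bears on this.

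The delayed-forest wording is a secondary inconsistency. It affects the comparison only if a control forest starts before the last assessment used. That is possible under section 3.8 if the study period is the twelve months of section 4.3, and does not arise on the 6- and 12-month schedule when section 3.1 is followed.

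**What to change.** State one control condition in the Abstract and sections 3.1 and 3.11, and say whether the forest commune receives the same nutritional education. Then choose one of two designs:

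- **Same education in all communes.** The arms then differ only by the forest package, and the estimate is the forest's effect in communes that also have education. The cost is delivering the education in the forest commune and amending section 4.2.
- **Education in control only.** Rename the comparator and word the objective and conclusion as forest versus nutritional education and support. The cost is wording and a narrower claim.

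Separately, align sections 3.1 and 3.11 on the delayed forest by tying its earliest start to the last assessment used in the comparison. This requires the follow-up schedules in the Abstract and sections 3.8, 3.10 and 4.3 to be reconciled first. If a control commune receives its forest earlier, record the start date and restrict the comparison to data collected before it. The cost is protocol wording, plus later visits dropped from the comparison if an early start occurs.
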